#### Strategies to improve adherence to interventions {11c}

To prevent loss of follow-up between combination therapies, both second TACE and RFA will be performed during a single hospital admission unless the patient is unable to undergo RFA due to severe postembolization syndrome.

#### Relevant concomitant care permitted or prohibited during the trial {11d}

According to the nationwide health insurance system, additional use of systemic chemotherapy is not reimbursed during locoregional treatment and its evaluation period (4–6 weeks). Although external radiation can be applied in patients with malignant portal vein thrombosis, this study will not include patients with portal vein thrombosis. Therefore, there is little chance of concomitant care during the intervention and evaluation period. After evaluation of the primary endpoint, other systemic or locoregional treatments can be applied according to patients’ disease status.

#### Provisions for post-trial care {30}

During the intervention period, patients will be closely monitored by investigators. Regular vital signs and biochemical laboratory tests will be performed. After the intervention and evaluation period, patients will undergo a conventional treatment course. Investigators will attempt to attenuate any damage from the interventions. When it is impossible to recover from irreversible injury, an insurance program associated with this trial will provide compensation. Patients will not be compensated for their participation in this trial. After evaluating primary endpoint, patients will be followed by their own treatment plan (local or systemic therapy) based on disease status.

#### Outcomes {12}

The primary endpoint is 4–6-week CR in patients with viable tumour after first TACE. Tumour response rate will be evaluated in accordance with mRECIST [8]. In patients with multiple tumours, the sum of the largest diameters of viable lesions will be calculated.

Secondary outcomes include the following: (1) progression-free survival, defined as the time between random allocation and first progression; (2) overall response rate, defined as CR + partial response; (3) number of treatments (i.e., TACE) until achieving CR; (4) overall survival rate (i.e., 6, 12, and 24 months) and cause of death; and (5) change in liver function within 6 months based on liver function tests and Child–Pugh score.

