**Assessments:**								
**Baseline MRI**	X							
**CT after first TACE**		X						
**Follow-up MRI**				X				
**Regular follow-up (lab, CT or MRI)**					X	X	X	X

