### Data collection and management

#### Plans for assessment and collection of outcomes {18a}

Consistent with the usual treatment course for HCC, initial laboratory tests and MRI will be performed. Tumour marker assessment (i.e., alpha-fetoprotein and protein induced by vitamin K absence-II) and MRI will also be performed 1 month after treatment. Blood laboratory tests and CTs will be performed depending on patients’ medical conditions as decided by the physician.

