### Statistical methods

#### Statistical methods for primary and secondary outcomes {20a}

Parametric data will be reported as mean and standard deviation. Non-parametric data will be reported as median and range. Independent sample *t*-tests or Mann–Whitney *U* tests for continuous variables and chi-square or Fisher’s exact tests for categorical variables will be used to compare treatment groups. For the primary endpoint, rate of CR will be compared using a chi-square test. For secondary endpoints, Kaplan–Meier survival analysis and log-rank tests will be performed. A *p*-value < 0.05 will be considered statistically significant.

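### The endpoint called progression-free survival does not count death, so as written it is time to progression; the two accounts of follow-up imaging also need reconciling

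*Protocol article*

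**What the plan says.** Outcomes {12} defines the first secondary outcome as "progression-free survival, defined as the time between random allocation and first progression". Objectives {7} names the endpoint without defining its event. Death appears only in a separate outcome, "overall survival rate (i.e., 6, 12, and 24 months) and cause of death".

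Statistical methods {20a} gives the analysis: "For secondary endpoints, Kaplan–Meier survival analysis and log-rank tests will be performed". It states no rule for deaths without progression and no competing-risk method.

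Imaging is described in two places:

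- Plans for assessment and collection of outcomes {18a} fixes one scan, "MRI will also be performed 1 month after treatment", and continues: "Blood laboratory tests and CTs will be performed depending on patients’ medical conditions as decided by the physician".
- Participant timeline {13} has a row beginning "Regular follow-up (lab, CT or MRI", marked at 2, 6, 12 and 24 months, after a follow-up MRI at 1 month. The row is not split by arm.

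On blinding, the hepatologist learns the allocation at randomisation and reveals it after the second TACE (Concealment mechanism {16b}; Procedure for unblinding {17b}). Who will be blinded {17a} says the independent outcome assessors are blinded. The reading procedure, two blinded radiologists with a third to settle disagreement, is set out only for the scan at 4–6 weeks.

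**The concern.** Progression-free survival ordinarily ends at progression or death, whichever comes first. An endpoint that ends only at progression is a different quantity. Under such a definition, a Kaplan–Meier analysis has nowhere to put a patient who dies without documented progression except among the censored, where that patient is treated as someone who could still progress later.

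Such deaths are plausible here. Child–Pugh scores up to 8 are eligible, the experimental arm adds an invasive procedure soon after embolization, and the data monitoring section foresees procedure-related death. If these deaths were more frequent in one arm, the result published as progression-free survival would not show it.

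An unseen analysis plan does not remove the problem. Censoring rules may properly sit there, but the event itself is fixed in this document. An analysis plan that followed it would inherit the wrong event, and one that did not would contradict it.

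The second issue is when progression is looked for. If CTs depend on the judgement of a physician who knows the allocation, progression could be found sooner in the arm scanned more often.

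**Working it through.** **The plan's own figures.** None is stated for progression-free survival. Sample size {14} rests on complete response alone. With 53% against 26%, two-sided α 0.05, 80% power and unpooled variance, n = (0.53×0.47 + 0.26×0.74) × (1.960 + 0.842)² / 0.27² = 0.4415 × 7.849 / 0.0729 = 47.5, so 48 per group, and 48 / 0.80 = 60. The figures reproduce and do not depend on the definition examined here.

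**Effect of leaving death out.** All inputs are assumptions: constant and independent hazards, control median time to progression 8 months, progression hazard ratio 0.65, 24 months of follow-up. The 60 per arm is the plan's.

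- Progression hazard, control: ln 2 / 8 = 0.0866 per month. Combination: 0.65 × 0.0866 = 0.0563.
- With deaths censored, the hazard ratio is 0.65 whatever the death hazards.
- With deaths counted, it is (0.0563 + d₁) / (0.0866 + d₀), where d₁ and d₀ are the monthly hazards of death without progression in the combination and control arms.
- Expected deaths as first event in an arm: 60 × [1 − exp(−24 × total hazard)] × d / total hazard.

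| d₀ (control) | d₁ (combination) | Hazard ratio, deaths counted | Deaths as first event, control / combination |
|---|---|---|---|
| 0.005 | 0.005 | 0.669 | 2.9 / 3.8 |
| 0.01 | 0.01 | 0.686 | 5.6 / 7.2 |
| 0.02 | 0.02 | 0.716 | 10.4 / 13.2 |
| 0.02 | 0.01 | 0.622 | 10.4 / 7.2 |
| 0.01 | 0.02 | 0.790 | 5.6 / 13.2 |
| 0.01 | 0.03 | 0.893 | 5.6 / 18.2 |

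As an example, the fifth row is (0.0563 + 0.02) / (0.0866 + 0.01) = 0.0763 / 0.0966 = 0.790. With equal death hazards the definition adds about 7 to 24 events (2.9 + 3.8 up to 10.4 + 13.2).

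Because the hazards are taken as independent, the table compares two different endpoints. It does not measure bias from informative censoring.

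**Effect of imaging.** A simulation assumed no true difference between arms, 60 per arm, a median time to progression of 6, 8 or 12 months, progression detected only at a scan, and a log-rank test at two-sided 0.05, with 2,000 runs per setting.

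| Scans | Rejection rate, range over the three medians |
|---|---|
| Both arms at 1, 2, 6, 12 and 24 months | 4.8% to 5.1% |
| One arm also at 9 and 18 months | 8.6% to 19.0% |
| One arm about every 3 months | 15.1% to 37.2% |

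The arm scanned more often appears to progress earlier. When both arms follow the timeline, the error rate is nominal.

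**The case against.** The wording defect is hard to dispute, but a reader might infer more than the document supports.

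*The scans are left to unblinded physicians.* The timeline marks CT or MRI at 2, 6, 12 and 24 months for all patients, and the 1-month MRI is fixed. The sentence on physician-decided CTs follows that fixed MRI and can be read as covering additional, clinically indicated scans. The outcome assessors are stated to be blinded. What stands is that the two sections do not agree on their face, that the gaps of 4, 6 and 12 months between scheduled visits leave room for unscheduled scans, and that the blinded reading procedure is not spelled out for later scans. Nothing in the document says scanning will differ by arm.

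*Treatment-related deaths would be hidden, or would even look like a benefit.* They would be missing from this one endpoint only. Overall survival with cause of death, CTCAE grading, reporting of grade 3 or higher events, and the data monitoring committee's power to recommend stopping all capture them. The illustration does not show a spurious benefit either: with independent hazards, censoring deaths leaves the progression comparison undistorted, and the larger shifts need assumed differences in death hazard between arms.

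*Deaths are censored.* This follows from a progression-only event analysed by Kaplan–Meier, but the document does not state it.

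**Conclusion.** The definition is wrong as written for the name it carries: the endpoint is time to progression. How much this matters depends on the frequency of death without progression, for which the document gives no figure. On the assumed inputs, the hazard ratio moves modestly, from 0.65 to between 0.67 and 0.72, when death hazards are equal. The full range when they differ is 0.62 to 0.89, so the difference can run in either direction.

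The imaging point is smaller. It is a discrepancy between two sections, and becomes a bias only if unscheduled scanning differs by arm.

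This should be corrected before analysis. It concerns one of five secondary outcomes. The primary comparison of complete response and the 120-patient sample size stand.

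**What to change.** 1. In Outcomes {12}, define progression-free survival as time from randomisation to first mRECIST progression or death from any cause, whichever comes first, with patients who have had neither event censored at their last evaluable scan. If the present definition is intended, rename the endpoint time to progression and treat death as a competing event in Statistical methods {20a}.
2. Reconcile Plans for assessment and collection of outcomes {18a} with Participant timeline {13}, so that progression is assessed on the same scheduled scans in both arms. State whether physician-decided CTs are additional to those scans.
3. State whether the blinded assessors also read the later scans for progression.

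The first change costs a sentence or two and no new data, because deaths and their causes are already collected. The second is also only wording if practice has followed the timeline. If scans have in fact been discretionary since recruitment began in November 2020, conduct would have to change and missed scans could not be recovered. Recruitment is expected to run to about June 2026, and the protocol provides for reporting amendments to the IRBs and the registry.

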**Methods:**

A total of 120 patients with beyond-the-Milan criteria HCC who have viable tumour after first TACE will be enrolled in this multi-institutional, parallel, pragmatic, randomized controlled trial. Patients with metastasis, vascular invasion, or a sum of tumour diameter > 8 cm will be excluded. Eligible patients will be randomly assigned to combination TACE and RFA therapy or TACE monotherapy groups. Patients in the combination therapy group will receive a second TACE and subsequent RFA at the viable tumour. Patients in the TACE monotherapy group will receive only second TACE. Patients in both groups will undergo magnetic resonance imaging 4–6 weeks after second TACE. The primary endpoint is 1-month tumour response, and secondary endpoints are progression-free survival, overall response rate, number of treatments until CR, overall survival, and change in liver function.

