#### After allocation

All patients will undergo second TACE for the viable portion of the HCC with ethiodized oil and Gelfoam particles. Interventional radiologists performing second TACE will be blinded to patient allocation, and TACE will be performed in a conventional manner.

Patients in the combination TACE and RFA therapy group will be treated with additional RFA of the viable portion of the tumour under the guidance of fusion images from ultrasound and CT. RFA will be implemented within 1–2 days after second TACE. Whether RFA can be delayed for up to 1 month will depend on the medical condition of the patients. RFA will be performed by physicians at the three hospitals with more than 8 years of experience. A 17-gauge radiofrequency electrode system including three electrodes with a length of 150 mm and a 30-mm ablation zone (Octopus; STARmed, Goyang-si, Korea) will be used. The number of electrodes used will be determined based on the size of the viable tumour and the physicians’ discretion. However, physicians will attempt to obtain an ablation margin of at least a 1-cm perimeter around the viable tumour.

Patients in the TACE monotherapy group will be discharged from the hospital without further intervention if they experience no AEs.

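### The treatments-to-CR outcome counts only TACE, so the RFA procedure that defines the combination arm goes uncounted

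*Protocol article*

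**What the plan says.** The protocol article names this secondary outcome in three places, with two meanings. The Abstract (Methods) lists it as "number of treatments until CR", and Objectives {7} uses the same unrestricted label. Outcomes {12}, which carries the definition, narrows it to "number of treatments (i.e., TACE) until achieving CR".

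The arms differ by one procedure. In the combination arm: "Patients in the combination therapy group will receive a second TACE and subsequent RFA at the viable tumour". In the other: "Patients in the TACE monotherapy group will receive only second TACE". The section After allocation describes RFA as its own procedure on a later day: "RFA will be implemented within 1–2 days after second TACE". It allows a delay of up to a month.

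Once the primary endpoint has been assessed, {11d} says that "other systemic or locoregional treatments can be applied according to patients’ disease status". This applies to both arms.

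On analysis, {20a} gives t-tests or Mann–Whitney tests for continuous variables, and then states: "For secondary endpoints, Kaplan–Meier survival analysis and log-rank tests will be performed". It does not say which of these applies to the treatment count. Sample size {14} states that data will be analysed by intention to treat.

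**The concern.** The definition leaves out the procedure that the trial is testing. A combination patient in CR after second TACE and RFA has had two procedures and scores 1. A monotherapy patient in CR after a second and a third TACE has also had two procedures and scores 2. A reader of the Abstract or the Objectives would take the result as the number of treatments needed to reach CR, and would credit the combination arm with fewer when part of that difference comes from what is counted.

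A second point is separate. A count up to CR has no completed value in a patient who never reaches CR, and the article does not say how such patients enter the comparison. Leaving them out would compare subsets selected by a post-randomisation outcome, at odds with the intention-to-treat statement.

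**Working it through.** **Inputs from the protocol.** CR rates of 53% (combination) and 26% (TACE alone), and 60 patients per group, all from Sample size {14}. That section states no figure for the treatment count. It gives the CR difference as 28 points, although 53 - 26 = 27; I use the two rates as printed. They do reproduce its sample size: (1.96 + 0.8416)² × (0.53×0.47 + 0.26×0.74) / 0.27² = 7.849 × 0.4415 / 0.0729 = 47.5, so 48 per group, and 48 / 0.80 = 60.

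**Assumptions (not in the protocol).** After the first post-randomisation course, each further course is one TACE with CR probability q = 0.10 to 0.40. There are at most K = 2 to 4 courses. Each combination patient has one RFA, in the first course, and monotherapy patients have none. Whether the pre-randomisation TACE is counted does not matter, since it adds one in both arms.

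**Formulas.** With first-course CR probability p, P(1) = p and P(k) = (1-p)(1-q)^(k-2) q for k ≥ 2.
- Mean among patients reaching CR: Σ k·P(k) / Σ P(k).
- Mean over all randomised patients: Σ k·P(k) + K·(1 - Σ P(k)).
- Counting RFA adds 1 in the combination arm.

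**Central case, q = 0.26 and K = 3.**
- Combination: P = 0.5300, 0.1222, 0.0904; sum 0.7426; Σ k·P = 1.0457. Mean among achievers 1.0457 / 0.7426 = 1.41. Mean over all patients 1.0457 + 3 × 0.2574 = 1.82.
- Monotherapy: P = 0.2600, 0.1924, 0.1424; sum 0.5948; Σ k·P = 1.0719. Mean among achievers 1.0719 / 0.5948 = 1.80. Mean over all patients 1.0719 + 3 × 0.4052 = 2.29.
- TACE only, achievers: 1.41 - 1.80 = -0.39.
- RFA counted, achievers: 2.41 - 1.80 = +0.61.
- RFA counted, all patients: 2.82 - 2.29 = +0.53.

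**Range (combination minus monotherapy).**

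| K | q | TACE only, achievers | RFA counted, achievers | RFA counted, all patients |
|---|---|---|---|---|
| 2 | 0.10 | -0.141 | +0.859 | +0.730 |
| 2 | 0.26 | -0.238 | +0.762 | +0.730 |
| 2 | 0.40 | -0.270 | +0.730 | +0.730 |
| 3 | 0.10 | -0.305 | +0.695 | +0.487 |
| 3 | 0.26 | -0.394 | +0.606 | +0.530 |
| 3 | 0.40 | -0.390 | +0.610 | +0.568 |
| 4 | 0.10 | -0.466 | +0.534 | +0.269 |
| 4 | 0.26 | -0.511 | +0.489 | +0.382 |
| 4 | 0.40 | -0.470 | +0.530 | +0.471 |

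With one course only (K = 1), the difference is 0 on the TACE count and +1 with RFA counted. The sign change is not universal: at K = 6 and q = 0.10, the all-patient difference with RFA counted is -0.105.

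**If RFA were worth no more than one extra TACE.** First-course CR in the combination arm would be 1 - 0.74² = 0.4524. The TACE-only difference among achievers would still favour combination, by 0.186, 0.298 and 0.379 at K = 2, 3 and 4.

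**Effect of restricting to achievers.** In the central case the TACE-only difference is 1.82 - 2.29 = -0.47 over all patients and -0.39 among achievers. The restriction therefore moves the result towards monotherapy, by 0.08 here and by about 0 to 0.27 over K = 1 to 4 and q = 0.10 to 0.40.

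**The case against.** **A TACE count may be intended.** Whether RFA spares repeat TACE is a fair question, and the Discussion notes that large tumours often need repeated treatment after TACE. The two procedures are normally given in one admission ({11c}), so a count of courses could also be defended. The protocol never says that the outcome measures total treatment burden. A count of all sessions also has a floor of two in RFA-treated patients, because RFA precedes the first assessment. All of this stands as a reason to report TACE sessions. It does not justify reporting them under an unrestricted label, and Outcomes {12} does not define a treatment as a course.

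**Offsets exist.** Later RFA or other non-TACE treatment in monotherapy patients is uncounted too, and the calculation assumes none. In the central case, about 0.61 such sessions per monotherapy achiever, with none added in the combination arm, would bring the all-session difference to zero.

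**Stronger readings that the protocol does not support.** A reader might infer that dropping patients without CR adds to the advantage of combination. The working shows that it slightly offsets it. A reader might also infer that the protocol plans a t-test or Mann–Whitney test in achievers only. It does not say so; {20a} names Kaplan–Meier and log-rank methods for secondary endpoints, which could be read as censoring the others, and an analysis plan not shown may settle this. Finally, the planning rates give about 32 of 60 (0.53 × 60 = 31.8) and 16 of 60 (0.26 × 60 = 15.6) in CR at 4–6 weeks. The remaining 28 and 44 are not patients lost to the analysis, since they can reach CR later during follow-up to 24 months.

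**Conclusion.** The point holds for the definition. Outcomes {12} is narrower than the Abstract and the Objectives, and it omits a procedure that the allocated treatment adds in one arm only. The understatement of at least one procedure per RFA-treated combination patient follows from the text without any model.

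How far this moves the comparison depends on later CR rates and course numbers that the protocol does not give. Over the assumed range of 2–4 courses and 10–40% CR per later course, the TACE-only difference favours combination by 0.14 to 0.51 treatments, and it changes sign when RFA is counted. Part of the TACE-only difference would reflect a genuinely higher first-course CR rate, so it should not be read as artefact throughout.

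Keeping patients without CR in the comparison is a separate matter of validity and not a source of bias towards combination. This is one of five secondary outcomes; the primary endpoint and the sample size do not depend on it.

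**What to change.** In Outcomes {12}, define the outcome as the number of all locoregional sessions (TACE, RFA and other) after randomisation until CR, counted the same way in both arms. Report the number of TACE sessions as a second, separately labelled count, so that any TACE-sparing effect remains visible. Use the same wording in the Abstract, Objectives {7} and Outcomes {12}.

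State that patients who never reach CR stay in the comparison, for example censored or ranked worst, in line with the intention-to-treat statement in {14}. A competing-risk analysis is possible, but the point does not require it.

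The cost is a wording change, a session count by type in the e-CRF (completed from medical records for patients already enrolled), and the report to the IRBs and registry that {25} requires for any change. Recruitment is still open, so the change can be made before the arms are compared. The drawback is that the result may look less favourable to the combination arm.

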#### Participant timeline {13}

**Table Tabb:** 

	**Study period**							
	**Enrolment**	**Allocation**	**Post-allocation**					**Close-out**
**Timepoint****	***-1 to -2 w***	**0**	***2 w***	***1 m***	***2 m***	***6 m***	***12 m***	***24 m***
**Enrolment:**								
**Eligibility screen**	X							
**Informed consent**	X							
**Laboratory tests**	X							
**Allocation**		X						
**Interventions:**								
**TACE + RFA**			X					
**TACE**			X					
**Assessments:**								
**Baseline MRI**	X							
**CT after first TACE**		X						
**Follow-up MRI**				X				
**Regular follow-up (lab, CT or MRI)**					X	X	X	X

